##### Primary endpoint

GV, defined as the standard deviation of the mean glucose level [17]. We will analyze whether the insulin administration route (intravenous and subcutaneous) affects the GV.

##### Secondary endpoints

Functional evaluation, analyzed by a researcher blinded to the experimental groups, at 24 h, 1 week and 4 weeks post-stroke. Motor and sensory performance will be evaluated using a variant of Rogers’ functional scale [23]. The beam walking test will evaluate hindlimb functions by testing the rats’ ability to traverse a wooden beam [23].Lesion size will be analyzed at 24 h and 4 weeks post-stroke by 7-T horizontal bore magnetic resonance imaging (MRI) (Bruker PharmaScan, Ettlingen, Germany), using T2-weighted (T2-W) spin-echo anatomical images, by a researcher who will be blinded to the experimental groups.Brain damage and repair-related markers will be analyzed at 4 weeks. The perilesional area of the brain will be studied in detail using immunofluorescence for superoxide dismutase 2, catalase, vascular endothelial growth factor (VEGF), brain-derived neurotrophic factor (BDNF), synaptophysin, glial fibrillary acidic protein, myelin basic protein and oligodendrocyte. Immunofluorescence images will be acquired by a researcher (who will be blinded to the experimental groups) using a Leica TCS-SPE confocal microscope (Leica Microsystems, Heidelberg, Germany). Plasma levels of damage and repair markers will be studied using Multiplex (eBioscience) and by ELISA (System Biosciences, Mountain View, CA, USA). The following markers will be analyzed: interleukin-1, interleukin-6, interleukin-10, vascular cell adhesion molecule, tumor necrosis factor alpha, matrix metalloproteinase 9, VEGF, BDNF, anti-Nogo A.

##### Sample size estimates

Based on data from previous studies [11, 25] and using the statistical software NCSS PASS 11 (NCSS, Utah, USA), we calculated that a sample of 10 rats per group will be required to achieve a power of 80% (1-beta) and a level of significance of 5% (alpha) to detect a significant effect of GV on the study endpoints.

### Statistical analysis

The statistical analysis will be performed with advice from the Department of Biostatistics of La Paz University Hospital. ﻿For the continuous variables, the following information will be provided: number of participants, mean, standard deviation, median, minimums, maximums and 25% and 75% quartiles. For the categorical variables, the frequency distribution and 95% confidence interval (CI), if applicable, will be provided. The analysis of the prognostic influence of GV on stroke outcomes will be performed in an exploratory manner without assumptions. We will first analyze GV as a continuous variable, comparing it with primary and secondary endpoints using Student’s t-test or the Mann–Whitney U test, as appropriate. We will also compare GV according to the various insulin types and administration routes applied to the patients according to the physician’s discretion. The comparisons will be performed with the one-way analysis of variance test. Secondly, we will perform a step forward logistic regression analysis for the endpoints that achieved a difference with a *P* value < 0.1 in the mean comparison tests, adjusting for age and baseline National Institutes of Health Stroke Scale score. The results will be expressed as odds ratios (OR) with 95% CI. In case of lack of homogeneity in the variances, we will use non-parametric tests (Kruskal–Wallis and Mann–Whitney test).

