**Methods:**

This translational study consists of two studies conducted in parallel: The first study is an observational, multicenter, prospective clinical study in which 340 patients with acute IS will be subcutaneously implanted a sensor to continuously monitor blood glucose levels for 96 h. The second study is a basic experimental study using an animal model (rats) with permanent occlusion of the middle cerebral artery and induced hyperglycemia (through an intraperitoneal injection of nicotinamide and streptozotocin). The animal study will include the following 6 groups (10 animals per group): sham; hyperglycemia without IS; IS without hyperglycemia; IS and hyperglycemia without treatment; IS and hyperglycemia and intravenous insulin; and IS and hyperglycemia and subcutaneous insulin. The endpoint for the first study is mortality at 3 months, while the endpoints for the animal model study are GV, functional recovery and biomarkers.

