##### Secondary endpoints

Modified Rankin Scale (mRS) and National Institutes of Health Stroke Scale. (NIHSS) at 3 months. These scales will be evaluated by a neurologist blinded to the GV values.Other GV measurements: coefficient of variation (CV), mean amplitude of glycemic excursions (MAGE); mean absolute glucose (MAG) rate of change [2, 17, 18]. CV is less influenced by mean glucose and is a good marker of hypoglycemia. A threshold value to define low and high GV using CV has recently been proposed [19]. MAGE and MAG are indexes used for studying glycemic variability in clinical trials, and normal references values for people without diabetes using CGM are available [18]. On the other hand, MAGE can provide information about the influence of the largest glycemic excursions.Neurological or systemic complications during follow-up. The following complications are pre-specified by protocol and will be checked at each visit: coma, seizures, early neurological impairment, brain edema, hemorrhagic transformation, recurrent strokes, acute coronary syndrome, pulmonary thromboembolism, respiratory infection, urinary infection, sepsis. Any other non-pre-specified complication reported during follow-up will be also recorded.

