##### Sample size estimates

Based on the data from the GLIAS-II study, [11] conducted in a similar setting and using nQuery Advisor software (Statistical Solutions Ltd., Cork, Ireland), we calculated that a sample of 340 patients will be required to achieve 80% statistical power and a confidence level alpha of 0.05 to detect a significant effect of GV on mortality at 3 months.

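### The stated alpha of 0.05 covers GV against 3-month mortality only, but two mortality time points are primary and every endpoint is tested unadjusted, so the plan should name its one inferential test

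*Protocol article*

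**What the plan says.** All places are in the protocol article, clinical study.

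- **Abstract, Methods.** One endpoint is named: "The endpoint for the first study is mortality at 3 months".
- **Sample size estimates.** The study is sized on that endpoint: "a sample of 340 patients will be required to achieve 80% statistical power and a confidence level alpha of 0.05", the purpose being "to detect a significant effect of GV on mortality at 3 months".
- **Primary endpoints.** GV is defined as the SD of glucose. The first 48 h after onset are the main analysis and 48-96 h is exploratory. Mortality is listed as primary at two time points, in hospital and at 3 months.
- **Secondary endpoints.** These are mRS and NIHSS at 3 months, then "Other GV measurements: coefficient of variation (CV), mean amplitude of glycemic excursions (MAGE); mean absolute glucose (MAG) rate of change", then neurological or systemic complications. For the last, "The following complications are pre-specified by protocol and will be checked at each visit: coma, seizures, early neurological impairment, brain edema" opens a list of 11 items, and any other complication is also recorded.
- **Statistical analysis.** The prognostic analysis is described as exploratory. Its first step is: "We will first analyze GV as a continuous variable, comparing it with primary and secondary endpoints using Student’s t-test or the Mann–Whitney U test". In the second step, "we will perform a step forward logistic regression analysis for the endpoints that achieved a difference with a" P value below 0.1, adjusting for age and baseline NIHSS. Results are odds ratios with 95% confidence intervals.

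**The concern.** The article gives three accounts of what is being tested. The abstract and the sample size point to 3-month mortality at alpha 0.05. The endpoint list makes two mortality time points primary and does not say which one decides. The analysis section declares the prognostic analysis exploratory, applies one unadjusted rule to every primary and secondary endpoint, and lets the first-step P value choose which endpoints get an adjusted odds ratio.

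If nothing is confirmatory, the alpha and power in the sample size have no test to attach to. If one test is confirmatory, the analysis section does not identify it. In either case a reader of the results could credit a 5% error rate to a conclusion that does not have it. Because adjusted results exist only for endpoints that pass the screen, the adjusted table would also tend to show the more favourable part of what was examined. Even the adjusted odds ratio for 3-month mortality depends on passing that screen.

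**Working it through.** **The plan's own figure.** N = 340 cannot be re-derived, because the article gives no mortality rate, SD of GV or effect size. Solving backwards with the two-means approximation (two-sided 0.05, 80% power), the detectable standardised difference is d = (1.960 + 0.842) × √(1/n1 + 1/n2), where n1 is the number of deaths and n2 = 340 − n1. At assumed mortality of 5%, 10%, 15% and 20%, d is 0.70, 0.51, 0.43 and 0.38. This only confirms that 340 fits a single test at 0.05. The article does not state sidedness; two-sided is assumed throughout.

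**Counts from the endpoint lists.**
- Primary mortality outcomes: 2, with in-hospital death contained in 3-month death (for deaths within 3 months).
- Scales: 2 (mRS, NIHSS).
- Complications: 1 if taken as one endpoint, 11 if each named item is tested.
- Total: 2 + 2 + 1 = 5, or 2 + 2 + 11 = 15.

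**Formula.** With k independent tests and no true effect, P(at least one P < α) = 1 − (1 − α)^k. For correlated tests, the test statistics are given a common correlation ρ through one shared normal factor, and the probability is integrated over that factor.

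**Two mortality tests.**
- Upper limit, independent: 1 − 0.95² = 9.75%.
- Nesting: two binary outcomes with rates p1 (in hospital) and p2 (3 months) correlate at √[p1(1 − p2) / (p2(1 − p1))]. With assumed rates of 5% and 10%, this is √(0.05 × 0.90 / (0.10 × 0.95)) = 0.69.
- The error is then 8.4%. It is 9.1% at ρ = 0.5 and 7.8% at ρ = 0.8, so about 8-9%.

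**All listed outcomes, SD of glucose only.**

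| Outcomes | ρ | At least one P < 0.05 | At least one P < 0.1 (passes the screen) |
|---|---|---|---|
| 5 | 0 | 1 − 0.95^5 = 22.6% | 1 − 0.9^5 = 41.0% |
| 5 | 0.5 | 18.3% | 33% |
| 15 | 0 | 1 − 0.95^15 = 53.7% | 1 − 0.9^15 = 79.4% |
| 15 | 0.2 | 49.7% | 75% |
| 15 | 0.3 | 45.7% | 71% |
| 15 | 0.5 | 36.1% | 59% |

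**Cohort check.** A simulated null cohort was also run: n = 340, 15 outcomes, assumed event rates of 1-40%, nested deaths, screening at 0.1 and then a severity-adjusted test at 0.05. It gave 45-53% for at least one adjusted P below 0.05. The adjusted step was a linear approximation to the logistic model.

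**The single test.** SD of glucose in the first 48 h against 3-month death, taken alone, keeps an error of 5%.

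**The case against.** The strongest reply is that the article already ranks its tests. The abstract names 3-month mortality, the Introduction hypothesises about mortality, the endpoint section fixes SD over 48 h as the main measure, and the sample size uses 3-month death. One sized test beside unadjusted exploratory results is an ordinary design, and multiplicity rules for secondary endpoints are often left to an analysis plan that is not shown here.

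Much of this stands. The missing adjustment of secondary outcomes is not in itself an error. What remains is what the article does state: two primary mortality time points against one sized test, an exploratory label that covers the sized test as well, and a P < 0.1 rule that decides which adjusted results exist.

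Two stronger readings are tempting, and the article does not support them.
- **Some outcome is more likely than not to be declared GV-related.** No section says that one significant outcome would meet the aim. With SD alone, the P < 0.05 figure exceeds one half only if 15 outcomes are counted and their correlation is low. Passing the P < 0.1 screen leads to a model and declares nothing.
- **All four GV indices are crossed with all outcomes, 60 tests in total.** The analysis section tests GV, which the article defines as the SD. CV, MAGE and MAG are listed as secondary endpoints, and their comparison with each outcome is nowhere stated.

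The count of 15 is itself one reading. Complications can be read as a single endpoint, which gives 5.

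**Conclusion.** The point holds in limited form. The alpha of 0.05 belongs to one test, and the article neither reserves the inference for that test in its analysis section nor settles which primary mortality time point decides. For the primary objective the excess is modest: about 8-9% instead of 5%, and never above 9.75%. Across all listed outcomes with SD only, the chance of at least one P < 0.05 under no effect is about 18-23% (5 outcomes) or 36-54% (15 outcomes).

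These ranges assume two-sided tests and a common correlation between test statistics of 0 to 0.5. The mortality figure assumes nested deaths at illustrative rates. None of the rates or correlations comes from the article. The figures show what an unranked reading of the results would risk; they do not show that the investigators intend such a reading.

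**What to change.** In Primary endpoints and in Statistical analysis, state that the only inferential test is SD of glucose in the first 48 h against 3-month mortality, in the model adjusted for age and baseline NIHSS, at two-sided 0.05. Fit that model whatever the first-step P value.

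Label in-hospital mortality, mRS, NIHSS, complications, CV, MAGE, MAG and the 48-96 h window as exploratory. Give estimates with confidence intervals and no significance claim. Report all of these results, not only those with P < 0.1.

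Holm or Benjamini-Hochberg adjustment of the secondary outcomes is optional. Spreading alpha over all 15 outcomes is not advised. At 0.05/15 = 0.0033 the critical value rises from 1.960 to 2.935, and power for mortality falls from 80% to Φ(1.960 + 0.842 − 2.935) = Φ(−0.133), about 45%.

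The cost is wording only, with no new patients or data. The downside is that fewer secondary results can be called significant.

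### The methods named for 3-month mRS and NIHSS imply a two-way split whose cut-point is not fixed; an ordinal analysis with death as the worst level would be more efficient and close the gap

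*Protocol article*

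**What the plan says.** The clinical Secondary endpoints section lists "Modified Rankin Scale (mRS) and National Institutes of Health Stroke Scale. (NIHSS) at 3 months", both as scales. The article gives no outcome cut-point for either. Its only mRS threshold is the pre-stroke score of 1 or less in Table 1, which is an eligibility rule.

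The Statistical analysis section gives one route for all clinical endpoints: "We will first analyze GV as a continuous variable, comparing it with primary and secondary endpoints using" a t-test or a Mann–Whitney test. Next, "we will perform a step forward logistic regression analysis for the endpoints that achieved a difference with a" P value below 0.1 "in the mean comparison tests, adjusting for age and baseline National Institutes of Health Stroke Scale score". And: "The results will be expressed as odds ratios (OR) with 95% CI". One further sentence names a multi-group test: "In case of lack of homogeneity in the variances, we will use non-parametric tests (Kruskal–Wallis and Mann–Whitney test".

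The same section calls the prognostic analysis exploratory. The clinical Sample size estimates section bases the 340 patients on 3-month mortality. Nothing says how a patient who has died enters the 3-month mRS or NIHSS analysis.

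**The concern.** A t-test or Mann–Whitney test with GV as the measured variable works only if the endpoint divides patients into two groups. That suits mortality and the complications. For two scales it requires a split that the article does not define. Three things follow.

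- **Power.** Collapsing an ordered scale to two groups discards information.
- **An open choice.** The cut-point can be picked after the data are seen. Because entry to the adjusted model depends on P < 0.1 in the two-group test, that choice also decides whether mRS or NIHSS receives an adjusted analysis at all.
- **Deaths.** NIHSS is scored by examining the patient, so no day-90 score can exist after death. The Introduction hypothesises that GV predicts death. If those patients were simply missing, the missingness would be linked to GV.

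**Working it through.** **1. The plan's own figure.** The 340 cannot be reproduced, because the article gives no effect size, GV standard deviation, death rate or sidedness. It can be shown to be attainable. With two-sided alpha 0.05 and 80% power, the detectable difference in GV between dead and alive is d = (1.960 + 0.842) × √(1/n_dead + 1/n_alive). At an assumed 10% mortality, n_dead = 34 and n_alive = 306, so d = 2.802 × √(1/34 + 1/306) = 0.51 SD. At assumed mortality of 5%, 15% and 20%, d is 0.70, 0.43 and 0.38 SD. This concerns mortality, a binary endpoint, and the present point leaves it untouched.

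**2. Cost of splitting the mRS.** Inputs: N = 340 (article). Assumptions: mRS has seven levels, 0–6, with death as 6 (the article does not spell this out); no covariates; GV standardised; a small effect with proportional odds.

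Information about the log odds ratio per patient:
- ordinal: (1 − Σp³)/3, where p are the level proportions;
- binary: q(1 − q), where q is the proportion at or above the cut.

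Relative efficiency (RE) is the second divided by the first. If the ordinal analysis has 80% power, binary power is Φ(2.802 × √RE − 1.960), and the N that restores 80% is 340/RE.

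Assumed distributions (%, mRS 0 to 6):
- A: 20/25/17/13/10/3/12
- B: 12/18/15/15/17/8/15
- C: 28/27/15/10/8/3/9

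Worked case, A cut at ≥3: Σp³ = 0.0335, ordinal information 0.3222; q = 0.38, binary information 0.2356; RE = 0.2356/0.3222 = 0.731; power = Φ(2.802 × 0.855 − 1.960) = 67%; N = 340/0.731 = 465.

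| Distribution | Cut | q | RE | Power of split | N for 80% |
|---|---|---|---|---|---|
| A | ≥2 | 0.55 | 0.768 | 69% | 443 |
| A | ≥3 | 0.38 | 0.731 | 67% | 465 |
| B | ≥2 | 0.70 | 0.645 | 61% | 528 |
| B | ≥3 | 0.55 | 0.760 | 69% | 448 |
| C | ≥2 | 0.45 | 0.779 | 70% | 437 |
| C | ≥3 | 0.30 | 0.661 | 63% | 515 |

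In each distribution the ordinal analysis reaches 80% power at an odds ratio of about 1.31 per SD of GV.

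Cross-check by simulation (1,500 runs, N = 340, odds ratio 1.3 per SD, assumed distribution 18/20/14/14/14/8/12): ordinal power 79%, power of 3–6 against 0–2 67%. The formula for that distribution gives RE = 0.2496/0.3252 = 0.77, in line with the simulation.

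**3. What would happen if deaths were left out of the NIHSS analysis.** This is conditional, since the article states no such rule. Simulation of 2,000 runs, N = 340, odds ratio 1.31 per SD of GV, with deaths taken as the worst tail of one latent severity scale:

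| Assumed mortality | Power, survivors only | Power, death ranked worst | Rank correlation, survivors only | Rank correlation, death ranked worst |
|---|---|---|---|---|
| 5% | 73% | 79% | 0.144 | 0.151 |
| 10% | 65% | 79% | 0.135 | 0.150 |
| 15% | 60% | 79% | 0.129 | 0.150 |
| 20% | 51% | 81% | 0.122 | 0.151 |

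The fall is more than a loss of numbers. At 10% mortality, 306 survivors with the correlation still at 0.15 would give 0.15 × √306 = 2.62 and power Φ(2.62 − 1.96), about 75%. The attenuated 0.135 gives 0.135 × √306 = 2.36 and about 66%, close to the simulated 65%.

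**The case against.** **The text does not commit to a dichotomy.** It says logistic regression, never binary; a proportional-odds model is also logistic and gives odds ratios. Kruskal–Wallis could compare GV across mRS levels. This stands in part: the split is implied, not stated. But Kruskal–Wallis appears only as a fallback for unequal variances, after the insulin comparison by analysis of variance, and it ignores the order of the levels. Nothing calls the logistic model ordinal, and the step that leads into it is a two-group test.

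**The stakes are limited.** Both scales are secondary endpoints in an analysis declared exploratory, and a dichotomised mRS is a legitimate summary. This stands, and it limits the weight of the point. It does not excuse leaving the cut-point open.

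**The figures rest on assumptions.** They do: the mRS distributions, effect size and death rates are all assumed, and the comparison is unadjusted whereas the plan adjusts for age and baseline NIHSS. The direction of the power loss does not depend on the particular distribution; its size does.

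**Two stronger readings are tempting and not supported.** A reader might infer that the 3-month NIHSS analysis excludes patients who died. The article is silent, a condensed article may leave this to the full protocol or analysis plan, and a dichotomised NIHSS could count deaths as a poor outcome. A reader might also infer that the functional results are biased. Splitting a scale costs precision but does not itself bias; attenuation would arise only if deaths were excluded.

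**Conclusion.** The point holds as a mismatch between the named methods and two of the endpoints. For 3-month mRS and NIHSS the plan implies a dichotomy with no cut-point. For mRS, under the three assumed distributions and cuts at 2 or 3, that keeps about 65–78% of the efficiency of an ordinal analysis: power of about 61–70% against 80%, or about 437–528 patients to recover 80%. These figures assume proportional odds, a small effect and no covariates. Separately, an unfixed cut-point allows a choice after the data are seen.

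The NIHSS part is a request to state a rule for deaths, not a finding that they are dropped. Only if they were excluded would the association be attenuated, by the amounts shown for 5–20% assumed mortality. Mortality as an endpoint and the 340 patients are unaffected. The change is worth making, because it needs only wording, but no confirmatory conclusion depends on it.

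**What to change.** Before outcomes are analysed against GV, amend the Statistical analysis section so that the two-group tests apply only to two-group endpoints (mortality, complications), and add:

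- **mRS at 3 months:** proportional-odds regression over 0–6 with death as 6, GV continuous, adjusted for age and baseline NIHSS, reported as a common odds ratio with 95% CI. Keep one dichotomy, fixed in advance (for example 0–2 against 3–6), as a supportive analysis.
- **NIHSS at 3 months:** a rank or ordinal method with death as the worst category. Label any survivors-only result descriptive.
- **Screening step:** say that these two models do not depend on P < 0.1 in a two-group test, since that test no longer applies to them.

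The cost is wording: no extra patients, visits or data. The downside is that the proportional-odds assumption must be checked and reported; the pre-specified dichotomy gives a fallback if it fails.

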##### Randomization

None (observational study).

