##### Intervention

After the participants sign the informed consent form, they will be implanted a CGM subcutaneously to monitor glucose levels for 96 h. These devices are of common use in the management of type 1 diabetes and they have been proven to be safe in stroke patients when used in research studies. Capillary finger prick glucose levels will be recorded every 4–6 h according to the standard protocols of each center, as well as the insulin administration characteristics (type, dose and route of administration) as per the treating physician’s criteria, following the local protocols for the in-hospital management of hyperglycemia. The treating physician and the nursing personnel will be blinded to the readings taken by the CMG device. All study centers will use the same brand of CGM (CE-marked). All patients will be managed according to current guidelines for acute stroke management and local protocols, including treatment with intravenous thrombolysis or mechanical thrombectomy if applicable. No laboratory data other than HbA1c will be collected for the study proposal. Any emergent laboratory abnormality during the study follow-up will be recorded as a complication.

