## DIscussion

To our knowledge, few studies have used continuous glucose monitors in acute IS [7, 8, 26–28]. A relationship has been found between GV (by means of the standard deviation of mean glucose levels) and infarct growth [8], as well as between GV and early neurological deterioration [29]. The main limitations of the prior studies using CGM in acute stroke are their monocentric settings, the lack of analysis of the effect of insulin administration on GV and the heterogeneity in the index used to express GV, given there is no widely accepted optimal index [30]. The GLIAS-III study is designed to overcome those limitations, with a prospective and multicenter approach, and is aimed at recruiting more than 300 patients. Moreover, the development of a parallel preclinical study using an animal model of permanent MCAO will increase our knowledge of the effect of insulin administration on GV, functional outcomes, lesion size, brain damage and repair-related markers.

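### The human comparison of glycemic variability by insulin type and route is fixed as an unadjusted one-way ANOVA, so it cannot separate insulin regimen from indication or centre practice

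*Protocol article*

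**What the plan says.** All references are to the protocol article.

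- **Comparison (Statistical analysis):** "We will also compare GV according to the various insulin types and administration routes applied to the patients", with the choice of insulin left to the physician.
- **Test (same section):** "The comparisons will be performed with the one-way analysis of variance test".
- **Fallback (same section):** "In case of lack of homogeneity in the variances, we will use non-parametric tests (Kruskal–Wallis and Mann–Whitney test".
- **The only adjusted model (same section):** "we will perform a step forward logistic regression analysis for the endpoints that achieved a difference with a" P value below 0.1. It adjusts for age and baseline NIHSS and yields odds ratios.
- **Allocation (clinical Randomization section):** "None (observational study".
- **How insulin is chosen (clinical Intervention section):** "as per the treating physician’s criteria, following the local protocols for the in-hospital management of hyperglycemia".
- **What is claimed:** the Introduction hypothesises that treatment regimens in routine practice may alter GV. The Discussion names "the lack of analysis of the effect of insulin administration on GV" among the limitations of earlier work that the study is designed to overcome.

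**The concern.** Insulin is given because glucose is high, and GV is computed from glucose over the same days. Patients with diabetes, higher HbA1c or higher early glucose are more likely to receive insulin and may also have wider swings whatever they receive. Centres may differ in both their insulin habits and their patients. A test without covariates assigns all of this to insulin group. Blinding staff to the continuous monitor does not break the link, because they still act on capillary readings taken every 4–6 h.

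The test is named in the article, so this is not a detail left for an analysis plan. At stake is the only human analysis described for the part of the hypothesis that concerns treatment regimens.

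**Working it through.** **1. Does any planned analysis adjust this comparison?**

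| Analysis | Outcome | Covariates |
|---|---|---|
| One-way ANOVA | GV by insulin type and route | none |
| Kruskal–Wallis / Mann–Whitney fallback | same | none |
| Forward stepwise logistic regression | endpoints passing P < 0.1, as odds ratios | age, baseline NIHSS |

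The logistic model, as written, does not model continuous GV by insulin group. Its named covariates also omit glucose level, HbA1c, diabetes, antidiabetic drugs and centre. The insulin comparison is therefore unadjusted throughout.

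**2. Are the likely confounders available?** HbA1c at baseline (Table 2), diabetes, pre-stroke antidiabetics and age (Data collection and management), baseline NIHSS (Table 2) and capillary glucose (Intervention) are all collected. Centre is known by design.

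**3. Is there a planned figure to reproduce?** None is given for this comparison. The sample size of 340 was set for GV and 3-month mortality, and nothing here depends on how it was derived.

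**4. How large could the distortion be? (illustration only)**

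From the article: N = 340 and alpha = 0.05. Everything else is assumed:

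- 60% receive no insulin, 30% subcutaneous and 10% intravenous, that is 102 subcutaneous and 34 intravenous patients.
- One standardised dysglycemia score has correlation γ with the latent choice of insulin (none, then subcutaneous, then intravenous) and correlation b with GV.
- The true effect of route is zero.

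*Closed form.* On the latent scale the intravenous group is the top 10%, with mean 0.1755/0.10 = 1.755. The subcutaneous group is the next 30%, with mean (0.3863 − 0.1755)/0.30 = 0.703. The gap is 1.052, so the expected spurious GV difference is d = γ × b × 1.052 SD.

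Example, γ = b = 0.5:
- d = 0.25 × 1.052 = 0.263 SD.
- Noncentrality = 0.263 × √(34 × 102/136) = 0.263 × 5.050 = 1.33.
- Chance of a significant result, two-sided 5%: about 26%.

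*Simulation,* 1000 replicates per setting. Ranges run over b = 0.3, 0.5, 0.7. Rates are percentages of studies with P < 0.05.

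| γ | Spurious IV − SC difference (SD) | ANOVA, IV vs SC | Kruskal–Wallis, IV vs SC | ANOVA, three groups | Linear model adjusted for the score, IV vs SC |
|---|---|---|---|---|---|
| 0 | about 0 | 4.2–5.9 | 4.1–5.3 | 4.4–5.1 | 4.1–5.1 |
| 0.3 | 0.10–0.21 | 8.3–19.2 | 7.8–18.2 | 20.4–83.6 | 4.4–5.0 |
| 0.5 | 0.15–0.36 | 11.7–46.9 | 12.7–46.2 | 54.7–100 | 4.5–5.5 |
| 0.7 | 0.225–0.505 | 21.4–80.6 | 20.0–77.9 | 84.2–100 | 4.3–6.3 |

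At γ = b = 0.5 the simulation gave 0.268 SD and 26.5%, in line with the closed form. The simulation error at a true rate of 5% is √(0.05 × 0.95/1000) = 0.7 percentage points, so adjusted rates of 4.1% to 6.3% are compatible with 5%.

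The rank test offers no protection, and including an untreated group makes a false signal more likely. The adjusted column is a best case: it adjusts for the one true confounder, measured without error.

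**The case against.** The strongest reply is that the article does not rest its question about insulin route on the human data. The formal aim on route belongs to the animal study, where rats are randomised and GV by route is the primary endpoint. The human comparison is not a listed endpoint and did not set the sample size. The sentence describing it says openly that insulin follows the physician's discretion. The Discussion credits the preclinical study with new knowledge on insulin and GV, and does not name the ANOVA.

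Much of this stands. A reader might infer that the human result will be presented as a causal effect of route. The article does not say so; that would be a prediction. What remains is that the hypothesis in the Introduction concerns routine clinical practice, and that the Discussion ties overcoming the earlier limitations to the prospective, multicenter approach before it turns to the animal work. The exploratory label in the Statistical analysis section applies to the prognostic value of GV for outcomes, not to this comparison.

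Three further inferences go beyond the text:

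- **Sicker patients get a different route.** The article does not say this. Route may follow centre habit, which is a reason to adjust for centre.
- **GV includes hours before the first insulin dose.** This is possible, but no window is stated for this comparison, and insulin may start before the sensor because inclusion is allowed up to 24 h after onset.
- **The ANOVA groups overlap.** The groups are not defined, and coding patients with more than one type or route is commonly left to an analysis plan that is not shown.

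**Conclusion.** The point holds as a fault in a supporting analysis. The article commits to an unadjusted comparison of GV between insulin groups formed by clinical choice, and no other planned analysis corrects it. A difference found this way may reflect indication or centre practice, so it cannot support the hypothesis that regimens alter GV or the claim to have closed the gap on insulin administration.

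The size is unknown. The 8% to 81% false-positive range for intravenous versus subcutaneous, with spurious differences of 0.10 to 0.51 SD, depends on the assumed group split and correlations and is illustrative only. The conclusion rests on the absence of any control for indication or centre, not on those figures. The change is worth making, but it leaves the GV–mortality analysis untouched.

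**What to change.** **Change.** In the Statistical analysis section, make the main insulin comparison a linear regression of GV on insulin group, on the log scale if GV is skewed. Use the 48 h window already defined for the main analysis. Adjust for first capillary glucose, HbA1c, diabetes, pre-stroke antidiabetics, age, baseline NIHSS and centre. Keep the ANOVA or Kruskal–Wallis test as description only. Report the results as adjusted associations, in the Discussion as well.

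**What to avoid.** Starting each patient's GV at the first insulin dose would give windows of different length, and the SD of a drifting glucose series depends on that length. A model with current route as a time-varying factor, adjusted only for baseline glucose, would leave confounding by later glucose, which responds to earlier insulin and drives the next choice.

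**Cost.** The wording of the analysis changes; no new data are needed. Intervals will be wider, especially where a centre uses one route only. Residual confounding remains. For patients given insulin before inclusion, the first capillary value may already reflect treatment, which should be stated as a limitation.
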